## Abstract

**Background:** Naoshuantong capsules (NC) are commonly used for the treatment of ischemic stroke. Experimental research and small-sample clinical trials have demonstrated that NC is effective in improving neurological recovery. Yet, there is a substantial lack of high-quality evidence on the precision treatment population of NC and long-term safety when making real-world clinical decisions. The acquisition of prospective longitudinal data in the real-world setting is essential to fully characterize the effectiveness and safety profile of NC for patients with ischemic stroke.

**Methods:** The Vital real-world Experience regarding Naoshuantong capsules for Unselected ischemic Stroke (VENUS) registry is a prospective, multicenter, observational study aiming to register 5,000 patients. Eligible adult patients diagnosed with ischemic stroke and newly treated with NC within 30 days of symptom onset will be consecutively registered from 84 participating sites across the Chinese mainland. Baseline data will be recorded at the patient registry, and all patients will be regularly followed up at 2, 4, 8, and 12 weeks after the initial patient registry, and 180 days after ischemic stroke onset. The primary outcome is the distribution of scores on the modified Rankin Scale at 12 weeks after initial patient registry. Adverse events will be recorded during the study for NC safety assessment.

**Results:** A total of 4,185 patients with ischemic stroke were enrolled, among which 37.06% patients were female. The average age of all patients was 65.22 years. The proportion of patients whose course of ischemic stroke was less than 14 days accounted for 93.45%.

**Conclusion:** The VENUS registry is designed to comprehensively document medical data regarding NC treatment for ischemic stroke in real-world settings. The findings of this study will provide valuable insights into the clinical management of patients with ischemic stroke and the subsequent outcomes of the use of NC when included in the best clinical practice.

Study registration: This study was registered with the Chinese Clinical Trial Registry (URL: http://www.chictr.org.cn/index.aspx, Unique identifier: ChiCTR1900025053).

## Introduction

Stroke is the second leading cause of death worldwide and the first leading cause of death in China, where the mortality is twice that of the global average (Zhou et al., 2019; GBD 2019 Stroke Collaborators, 2021). Stroke leads to disabilities, and the recurrence of stroke must not be ignored (Coull et al., 2004; Chen et al., 2020). Stroke-related treatments and post-stroke care result in heavy economic burden. China has been reported to bear the highest economic burden related to stroke (Wang et al., 2017; Rajsic et al., 2019). The estimated lifelong risk of stroke is approximately 39.3% in China (GBD 2016 Lifetime Risk of Stroke Collaborators, 2018). Ischemic stroke (IS) is the main subtype of stroke accounting for 70–83% of all cases in China according to different survey data (Wang et al., 2017; Gu et al., 2021).

Although evidence-based interventions have been advocated in China, unavoidable gaps between guideline recommendations and clinical practice remain. These gaps may be attributed to the influence and challenge of known or unknown confounding factors or objective difficulties in real-world settings. Reperfusion treatment such as intravenous thrombolysis and endovascular treatment has been proven to improve functional outcomes of patients with acute ischemic stroke, but only a minority of highly selected patients could benefit from these treatments (Powers et al., 2019). Antiplatelet, lipid-lowering, and antihypertensive therapies make up the cornerstone of secondary prevention of IS, though irreversible aspirin or clopidogrel resistance of individuals and poor long-term medication compliance weaken the net benefit of recommended medicines (Wei et al., 2010; Wang et al., 2016; Girot et al., 2020). Therefore, there is an unmet need to investigate safe and effective therapies for IS when the optimal treatments are ineligible.

Naoshuantong capsules (NC) are a combination of five natural herbal ingredients that are widely used for the treatment of IS in China. Preclinical studies regarding their mechanisms have demonstrated that NC reduces the cerebral infarct area and attenuates neurological deficits *via* inhibiting neuronal apoptosis, suppressing the overexpression of inflammatory cascade injuries, attenuating the neurotoxicity of excitatory amino acids, and increasing hemorheology and cerebral energy metabolism (Xiang et al., 2010; Liu et al., 2014; Luo et al., 2020). These results have indicated that the efficacy of NC is based on a synergistic effect of several components, targets, and pathways. A systematic review of randomized controlled trials (RCTs) regarding the clinical efficacy and safety of NC reported benefits in alleviating neurological impairments and improving activities of daily living with 1–12 months of treatment in patients with IS.

However, unaddressed issues concerning NC treatment for IS in real-world practice limit its optimal usage. The epidemiology and clinical characteristics of patients with IS who undergo NC treatment remain unclear. RCTs that have reported the efficacy of NC included highly selected patients and excluded special populations such as elderly patients or patients with severe comorbidities, resulting in little data regarding the effects of NC in these populations. Additionally, the benefits and harms of NC for patients with IS should be interpreted with caution, as the RCTs were conducted under relatively ideal conditions without confounding factors, and a high risk of bias exists, challenging the robustness of the results regarding the efficacy and safety of NC (Zhang et al., 2019). The long-term effects of NC, such as the effects on functional status or stroke recurrence in patients with IS, remain uncertain due to a lack of data. The optimal time point for initiating NC treatment, proper dosage, and treatment course are yet to be verified. Although encouraging data have indicated the clinical safety of NC, the long-term safety in large-scale populations has not been investigated.

A prospective, multicenter registry with regular and long-term follow-up will provide the much-needed data regarding the use of NC in patients with IS. Therefore, the Vital real-world Experience regarding Naoshuantong capsules for Unselected ischemic Stroke (VENUS) registry has been developed to generate sociodemographic and medical data related to patients with IS who undergo NC treatment and to evaluate the effectiveness and safety of NC for patients with IS in a real-world setting.

## Methods and design

### Study design

The VENUS registry (registered with the Chinese Clinical Trial Registry, unique identifier: ChiCTR1900025053) is a prospective, multicenter, post-marketing, observational study designed to provide insight into the administration of NC for patients with IS in the real-world setting. The specific aims of the VENUS registry are to 1) systematically investigate the effectiveness of NC for patients with IS and explore any effectiveness difference among NC user cohorts with distinct clinical characteristics; 2) to observe the long-term safety profile of NC and probe potential risk factors *via* regular continuous follow-ups; 3) to establish a database for further nested studies with specific predefined hypotheses to facilitate novel knowledge discovery. An overview of the VENUS registry flowchart is shown in Figure 1. This study was approved by the institutional review board of the leading center, Dongzhimen Hospital, Beijing University of Chinese Medicine, Beijing, China (No. DZMEC-KY-2019-10), and was approved by the local institutional review boards of all participating sites.

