### Study population

In order to achieve a high population representation, we registered patients with a unstrict inclusion criterion. All adult patients (≥18 years) admitted to the participating sites with a clear diagnosis of IS according to the guideline were screened. Patients who were newly treated with NC within 30 days of symptom onset were consecutively included in this study. Patients with other complications that hinder the assessment of neurological function and disability will be excluded. Patient participation is entirely voluntary and written informed consent that complies with the Declaration of Helsinki principle will be obtained from all patients or their legally authorized representatives.

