### Follow-up procedures

The research personnel will regularly perform face-to-face or telephone follow-ups at 2, 4, 8, and 12 weeks after the initial patient registry, and 180 days after IS onset. Information including death, recurrent stroke events, and adverse events will be obtained during the whole study. Details of the follow-up timetable on life dependency, neurological impairment, activities of daily living, cognitive functions, and Chinese medicine syndrome collection are as follows: 1) assessment of mRS will be conducted at all follow-up time points mentioned previously; 2) assessment of DSSEIS, NIHSS, and MMSE will be conducted at 2, 4, 8, and 12 weeks after patient registry; 3) assessment of BI will be conducted at 2, 4, and 8 weeks after patient registry. The aforementioned blood samples will be collected again from 40 patients, at 4 weeks after patient registry. Adherence to the NC treatment and medicine combination will be recorded at 2, 4, 8, and 12 weeks after patient registry. The results will be recorded if the patients receive examination with regard to laboratory tests, magnetic resonance imaging (MRI) or computed tomography (CT), and transcranial Doppler sonography. Death will be confirmed by a death certificate. Recurrent stroke events leading to rehospitalization will be confirmed by discharge diagnosis while suspected recurrent stroke events will be determined by the endpoint judgment committee when without hospitalization (Feng et al., 2021). Adherence to the NC treatment will be defined as the proportion of prescribed doses taken (Osterberg and Blaschke, 2005).

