### Study outcomes

The primary outcomes of the VENUS registry is the changes of life dependency measured with the distribution of scores on the mRS at 12 weeks after initial patient registry. The secondary outcomes are measured with different indicators those will be assessed at subsequent follow-up visits, such as changes in neurological impairment, long-term safety, improvements in neurological function, improved activities of daily living, favorable functional status, changes in cognitive functions, all-cause mortality, recurrent stroke events, and adherence to NC treatment. In addition, we will exploratively detect the biological outcomes by using the RayBiotech human inflammatory factor antibody array Q3 (RayBiotech, Inc., QAH-INF-3-1) to profile the variations of the inflammatory indicators in the blood samples. The detailed study outcomes of the VENUS registry are illustrated in Table 1.

**TABLE 1 T1:** Complete outcomes of the VENUS registry.

Primary outcome
Distribution of scores on mRS at 12-week follow-up
Secondary outcome
Change in the NIHSS score between baseline and 4-week follow-up
Recurrent stroke events (ischemic stroke, hemorrhagic stroke which includes intracerebral hemorrhage and subarachnoid hemorrhage) within 2-week, 4-week, 8-week, 12-week, and 180-day follow-up
Composite end points of recurrent stroke events and death within 2-week, 4-week, 8-week, 12-week, and 180-day follow-up
Proportion of patients with an mRS score ≤2 at 2-week, 4-week, 8-week, 12-week, and 180-day follow-up
Distribution of scores on mRS at 2-week, 4-week, 8-week, and 180-day follow-up
Proportion of patients with the BI score ≥90 at 2-week, 4-week, 8-week, 12-week, and 180-day follow-up
Change in the NIHSS score between baseline and 2-week, baseline and 8-week, baseline and 12-week, baseline and 180-day follow-up
Proportion of patients with the BI score ≥90 at 4-week and 180-day follow-up
NC treatment duration within 2-week, 4-week, 8-week, 12-week, and 180-day follow-up
MMSE scale score at 2-week, 4-week, 8-week, 12-week, and 180-day follow up
All-cause mortality within 12-week and 180-day follow-up
Incidence of adverse events during the whole study
Exploratory outcome
^a^Variation of inflammatory indicators between baseline and 4-week follow-up

Abbreviations: mRS, modified Rankin scale; NIHSS, National Institute of Health Stroke Scale; BI, Barthel Index; MMSE, Mini-Mental State Examination; NC, Naoshuantong capsules.

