**FIGURE 3 F3:**
[figure not shown]
Patient enrollment flowchart.

Patient demographic characteristics are presented in Table 2. Overall, 37.06% of patients were female. The average age at IS onset was 65.22 years. As for the risk factor distribution among the patients, 21.34% were current smokers, and the proportions of overweight or obesity were 42.01% and 8.75%, respectively. Hypertension was the most frequent complication and occurred in 62.37% of patients. And 24.01% of patients had diabetes mellitus, 14.19% had coronary heart diseases, and 8.77% had dyslipidemia. The proportion of patients whose course of IS was less than 14 days accounted for 93.45%, and the IS course ranged from 15 to 30 days which accounted for 6.55%. With regard to the distribution of TOAST classification, more than half of the patients had large artery atherosclerotic strokes, 34.43% had small artery occlusions, 1.98% had cardioembolic strokes, and 8.63% had stroke of the undetermined cause or other causes. Patients with an NIHSS score less than or equal to 3 accounted for 51.62% of all IS cases. In terms of the distribution of syndrome elements in IS, the internal-wind element accounted for the majority, while the yin-deficiency syndrome element, which frequently emerges during recovery or sequelae period of stroke, accounted for the smallest proportion.

**TABLE 2 T2:** Baseline characteristics of the registered patients in the VENUS study.

Characteristic	(N = 4,185)
Age (yr), mean ± SD	65.22 ± 11.12
Gender, *N* (%)	
Male	2,634 (62.94)
Female	1,551 (37.06)
Ethnicity, *N* (%)	
Han	4,152 (99.21)
non-Han	33 (0.79)
BMI, *N* (%)	
Lean (≤18.4 kg/m^2^)	114 (2.72)
Normal (18.5–23.9 kg/m^2^)	1,947 (46.52)
Overweight (24–27.9 kg/m^2^)	1,758 (42.01)
Obese (≥28 kg/m^2^)	366 (8.75)
Education, *N* (%)	
Elementary or below	2,037 (48.67)
Middle school or high school	1,864 (44.54)
College degree	220 (5.26)
Undergraduate or above	64 (1.53)
Types of health insurance, *N* (%)	
Basic health insurance scheme	2,473 (59.09)
New cooperative medical system	1,526 (36.46)
Public medical insurance	36 (0.86)
Commercial insurance	12 (0.29)
Self-payment	138 (3.30)
Course of ischemic stroke, *N* (%)	
≤14 days	3,911 (93.45)
15–30 days	274 (6.55)
TOAST classification, *N* (%)	
Large artery atherosclerosis	2,300 (54.96)
Cardioembolism	83 (1.98)
Small artery occlusion	1,441 (34.43)
Stroke of other determined etiology	66 (1.58)
Stroke of undetermined etiology	295 (7.05)
Past medical history, *N* (%)	

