## Discussion

The current evidence regarding the clinical management of IS with NC has been mainly derived from RCTs. The strict selection criteria of participants within these trials limit the generalizability of the results regarding NC effectiveness in real-world practice. Generating evidence with high internal validity that is adaptive to routine clinical practice is necessary. A well-designed, large-scale registry of patients with IS merits strong attention from clinicians and clinical investigators, due to its emphasis on the association of effectiveness, benefits, and disadvantages of investigated treatment methods with long-term clinical outcomes in the real-world setting (Kim et al., 2014). In this study, the rationale and design of a prospective, multicenter, registry-based observational study with an unstrict selection criteria for target patients that aims to generate sociodemographic and medical data regarding the use of NC treatment in patients with IS are described. The benefit–harm profile of NC for patients with IS can be determined using this registry and included in updated recommended treatment guidelines.

NC is an oral Chinese medicine, and the proper use of Chinese medicine is based on the unique theory system, namely, holism and syndrome differentiation. The core concept of Chinese medicine syndrome differentiation lies in individualized treatment (Yuan, 2021). Discovering the crucial factors influencing clinical outcomes through complex and diversified information and delivering targeted medicine are important to balance the benefits and harms of specific treatments, and to maximize the net clinical benefit, achieving individualized treatment with Chinese medicine. Multidimensional data regarding NC treatment for different clinical characteristics of patients with IS in view of the Chinese medicine theory will be collected, and the corresponding effects on clinical prognosis will be explored in this registry. These results will help advance the accurate treatment of IS with NC in the theoretical system of Chinese medicine.

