The global spread of the COVID-19 outbreak has presented huge challenges for public health and for conducting clinical research in terms of patient compliance and follow-up; therefore, patient enrollment is slightly delayed when compared to the anticipated completion time to ensure continuity, completeness, and accuracy of the data. As such, 4,981 patients have been enrolled in the study, of which 4,185 have been included in the final analysis. The study profile and baseline characteristics of the patients were reported. According to the current data analyses, VENUS and CNSR-III have a similar severity distribution of neurological deficits evaluated by NIHSS (Wang et al., 2019). Compared to previous national stroke registries, the VENUS registry is exclusive as it allows for the evaluation of evolution of syndrome elements at different time points of IS, which contributes to targeted, personalized precision therapy for IS based on syndrome differentiation. Moreover, the VENUS registry is closer to clinical practice in the real-world setting than rigorous RCTs. According to the current statistical analysis of baseline information, the internal-wind element comprises the largest proportion, which could be rationally explained by 93.73% of patients in the acute phase of IS and is consistent with the findings of previous studies (Xin et al., 2016). Similar to other observational registry studies, selective biases in the VENUS registry are unavoidable although the targeted sample population covers a relatively larger number of regions in the Chinese mainland (Ohman et al., 2006; Venketasubramanian et al., 2015). However, cross-sectional and longitudinal data from the multicenter participation and regular sequential follow-ups of registered patients are planned, and both the geographical and temporal characteristics of patients with IS can be explored to improve the representation of the study findings. Furthermore, special populations (such as elderly patients or patients with severe comorbidities) who are normally excluded from clinical trials will be registered based on the unstrict inclusion criteria of this registry, increasing the generalizability of the results in real-world settings. Strict quality control in terms of research personnel training and timely audits will be conducted before study initiation to ensure the accuracy and completeness of the collected data. In addition, the VENUS registry will support the establishment of a database for further individual patient data pooling as per homogenous investigational variables with that of the China Stroke Registry for Patients with Traditional Chinese Medicine (CASES-TCM) study, embedding comparative effectiveness research, pragmatic randomized clinical trial, or nested case–control study to generate secondary hypotheses for extra validation in clinical trials (Feng et al., 2021).

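### All patients take NC and the article links syndrome elements to stroke phase, so cohort differences in change from the registry baseline may reflect time since onset and prognosis rather than a differential NC effect

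*Protocol article*

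**What the plan says.** - **Aim.** Study design sets out to "explore any effectiveness difference among NC user cohorts with distinct clinical characteristics". Syndrome elements are not named there. The Discussion supplies the link: "Multidimensional data regarding NC treatment for different clinical characteristics of patients with IS in view of the Chinese medicine theory will be collected", with personalised therapy by syndrome as the stated purpose.
- **Entry.** Study population: "Patients who were newly treated with NC within 30 days of symptom onset were consecutively included in this study". No cohort without NC is described.
- **Clock.** Follow-up procedures: "telephone follow-ups at 2, 4, 8, and 12 weeks after the initial patient registry, and 180 days after IS onset". The primary outcome is the mRS distribution at 12 weeks after registry. The first secondary outcome in Table 1 is "Change in the NIHSS score between baseline and 4-week follow-up". Only the last visit is timed from onset.
- **Elements and phase.** Result: "the yin-deficiency syndrome element, which frequently emerges during recovery or sequelae period of stroke, accounted for the smallest proportion". Discussion: "the internal-wind element comprises the largest proportion, which could be rationally explained by 93.73% of patients in the acute phase of IS".
- **Adjustment.** Statistical analysis plans multivariable regression with unnamed covariates and propensity score matching. Time from onset to registry is not mentioned.

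**The concern.** Neurological deficit after ischaemic stroke falls fastest early on. If one cohort tends to be registered later than another, part of its recovery has already happened before its baseline, and its change from baseline will be smaller even if NC does nothing. The article treats internal-wind and yin-deficiency as partly markers of phase, so a syndrome-element comparison is exposed to exactly this imbalance.

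There is also a limit that no choice of clock removes. Because everyone takes NC, a difference in outcome between cohorts mixes any difference in NC effect with the cohorts' own prognosis. Regression and matching can balance measured characteristics between cohorts of NC users. They cannot supply the missing contrast with similar patients not taking NC. A cohort could be named as the one that responds best to NC when it was only registered earlier or had a better outlook.

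**Working it through.** **1. The article's own figures.** From Table 2, 3,911/4,185 = 93.45% had a course of at most 14 days and 274/4,185 = 6.55% a course of 15–30 days. The flow in Result also reproduces: 4,981 − 266 − 297 − 172 − 21 − 40 = 4,185. The acute-phase share of 93.73% in the Discussion does not match Table 2: 0.9373 × 4,185 ≈ 3,923, against 3,911. The two should be reconciled, but nothing below depends on it.

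**2. How far elements can differ in phase (counting bounds, Table 2).**
- Yin-deficiency, 756 patients: at most 274/756 = 36.2% can be past day 14, so at least 482 (63.8%) were at or before day 14.
- Internal-wind, 2,940 patients: at most 274/2,940 = 9.3% can be past day 14.
- At least 3,911 − 2,940 = 971 of the 3,911 early patients (24.8%) lack internal-wind.

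The link to phase can therefore be real but is far from complete.

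**3. Overlap.** 2,940 + 1,189 + 1,291 + 1,182 + 1,767 + 756 = 9,125 element counts; 9,125/4,185 = 2.18 per patient.

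**4. Four-week change with no NC effect.** The documents give no recovery curve and no distribution of registry day. Assume the recoverable deficit decays as exp(−t/τ), with τ = 7, 14 or 30 days. The part recovered in the 28 days after registry on day d is F(d) = exp(−d/τ) − exp(−(d+28)/τ).

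*(a) Through the 15–30 day group.* Assume early patients register on day 3 or 7 and late ones on day 22. Let s be the late share among yin-deficiency patients and w = (274 − 756s)/3,429 the late share among the others. The relative shortfall for yin-deficiency is (s − w)[F(early) − F(22)] / [(1 − w)F(early) + wF(22)].

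| Late share in yin-deficiency | w | Shortfall |
|---|---|---|
| 6.5% (equal) | 6.5% | 0% |
| 13.1% (doubled) | 5.1% | 3.2–7.8% |
| 19.6% (tripled) | 3.7% | 6.4–15.5% |
| 36.2% (maximum) | 0% | 14.3–33.8% |

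Example (maximum, day 3, τ = 7): 0.362 × (0.640 − 0.042)/0.640 = 0.338.

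*(b) Within the first 14 days.* For registry days d1 < d2 the relative shortfall is 1 − exp(−(d2 − d1)/τ). Day 3 versus 7: 12% (τ = 30) to 44% (τ = 7). Day 3 versus 10: 21% to 63%.

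*(c) In NIHSS points, for one hypothetical patient.* Assume NIHSS 6 at onset, a plateau at 40% or 60% of that, and τ of 10, 20 or 30 days. The 4-week change is 1.4–3.1 points from a day-1 baseline and 0.6–1.4 from a day-14 baseline. With the same curve for both, the difference is 0.5–2.2 points. These are single-patient contrasts, not cohort means.

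**5. Twelve-week mRS.** Registry on day 0–30 puts this visit on day 84–114 after onset. With the curve of step 4, the recoverable deficit still open is exp(−84/τ) versus exp(−114/τ), at most 6.1% versus 2.2% (τ = 30), a gap of 3.9 percentage points. The unadjusted score is little affected.

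Adjustment for baseline score changes this. Take the model of step 4(c), with plateau fraction f, as a generic deficit score. The share of the baseline deficit left 84 days later is [f + (1 − f)exp(−(d+84)/τ)] / [f + (1 − f)exp(−d/τ)]. It is 42–63% for day-1 entry and 55–86% for day-14 entry. On the same curve the gap is 9–31 percentage points. Adjusting for baseline without time since onset can thus bring the problem back.

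**The case against.** - **The dominant-bias reading is not shown.** A reader might infer that cohort differences would consist largely of natural recovery. Only 6.55% of patients were in the 15–30 day class, most yin-deficiency patients were at or before day 14, and equal late shares give no bias by that route. The larger range in step 4(b) rests on registry days that are assumed, and step 4(c) compares individuals. This stands: the size is unknown.
- **The primary outcome is hardly touched.** This stands for the unadjusted 12-week mRS. It does not carry over to change from baseline or to baseline-adjusted analyses, and Study outcomes itself describes the primary outcome in terms of change.
- **Adjustment is planned, and covariate lists belong in an analysis plan.** Time since onset could well be among the covariates, so its absence from the article would not be a finding by itself. Nor does the article say that the two-class onset split, a descriptive row of Table 2, will be the covariate. What remains is that no covariate list turns a comparison among NC users into a comparison of NC effects.
- **Some apparent targets are not planned analyses.** The Introduction remarks "The optimal time point for initiating NC treatment, proper dosage, and treatment course are yet to be verified", but that is a stated evidence gap and not one of the aims. No section says that the elements will be analysed as exclusive groups. Both objections stand.
- **The aim is exploratory and the article knows that elements change.** Also true: the syndrome scale is repeated at 2, 4, 8 and 12 weeks. That supports the view that the elements depend on time.

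**Conclusion.** The point holds in a limited form. The aim speaks of effectiveness differences among cohorts who all take NC; the article links some syndrome elements to stroke phase; and NIHSS change starts at a registry day that may lie up to 30 days after onset. Differences between cohorts in change from baseline, the 4-week NIHSS change above all, could therefore reflect time since onset and prognosis.

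Under the assumed curves, the relative gap with no NC effect runs from 0% to 34% through the late entrants, and from 12% to 63% for the assumed day contrasts inside the first 14 days. The actual size cannot be given without registry day by element. The documents do not support saying that natural recovery would account for most of any difference, nor that the unadjusted 12-week mRS is seriously distorted.

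**What to change.** 1. Describe differences between NC-user cohorts as prognostic associations among NC users, not as differences in effectiveness.
2. In cohort comparisons of change, or of outcomes adjusted for baseline, include days from onset to baseline as a continuous flexible term (for example a spline) together with the baseline score. Report the distribution of onset-to-registry time by syndrome element, so that the imbalance can be seen.
3. Show the 180-day mRS alongside. It is timed from onset and already a secondary outcome. Table 1 also lists NIHSS, BI and MMSE at 180 days, but Follow-up procedures schedules only the mRS then, so the mRS is the functional measure on which both sections agree.
4. If syndrome elements are compared, enter all six jointly as present/absent terms in one model, because they overlap.

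No new data should be needed: the visit schedule already requires the onset and registry dates, provided the onset date is held as a date. The cost is a few degrees of freedom and a more modest claim.
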